## Abstract

**Background:**

Mortality rates in the Intensive Care Unit and subsequent hospital mortality rates in the UK remain high. Infections in Intensive Care are associated with a 2–3 times increased risk of death. It is thought that under conditions of severe metabolic stress glutamine becomes "conditionally essential". Selenium is an essential trace element that has antioxidant and anti-inflammatory properties. Approximately 23% of patients in Intensive Care require parenteral nutrition and glutamine and selenium are either absent or present in low amounts. Both glutamine and selenium have the potential to influence the immune system through independent biochemical pathways. Systematic reviews suggest that supplementing parenteral nutrition in critical illness with glutamine or selenium may reduce infections and mortality. Pilot data has shown that more than 50% of participants developed infections, typically resistant organisms. We are powered to show definitively whether supplementation of PN with either glutamine or selenium is effective at reducing new infections in critically ill patients.

**Methods/design:**

2 × 2 factorial, pragmatic, multicentre, double-blind, randomised controlled trial. The trial has an enrolment target of 500 patients. Inclusion criteria include: expected to be in critical care for at least 48 hours, aged 16 years or over, patients who require parenteral nutrition and are expected to have at least half their daily nutritional requirements given by that route.

Allocation is to one of four iso-caloric, iso-nitrogenous groups: glutamine, selenium, both glutamine & selenium or no additional glutamine or selenium. Trial supplementation is given for up to seven days on the Intensive Care Unit and subsequent wards if practicable. The primary outcomes are episodes of infection in the 14 days after starting trial nutrition and mortality. Secondary outcomes include antibiotic usage, length of hospital stay, quality of life and cost-effectiveness.

**Discussion:**

To date more than 285 patients have been recruited to the trial from 10 sites in Scotland. Recruitment is due to finish in August 2008 with a further six months follow up. We expect to report the results of the trial in summer 2009.

**Trial registration:**

This trial is registered with the International Standard Randomised Controlled Trial Number system. **ISRCTN87144826**

## Background

Intensive care unit (ICU) and subsequent hospital mortality in the UK remains high, with figures of 15–20% and 30% respectively [1]. The cost per ICU bed-day exceeds £1,100 based on a mean from all trusts in England and Wales [2]. In many countries, including the UK, provision of intensive care is inadequate to meet demand. Infections acquired on the ICU have been associated with a two to three fold increased risk of death [3], this is associated with both illness and drug related impairment of the patient's immune system. Multiple portals for infection include: tracheal tubes, nasogastric tubes, chest and abdominal drains, central venous, pulmonary arterial and urinary catheters, wounds, and infective loci present before admission to ICU. These infections increase mortality, morbidity, length-of-stay, antibiotic usage and costs of care. As a result 40–50% of patients on ICU are prescribed antibiotics at any one time [2]. Such concentrated antibiotic usage may contribute to ICU, hospital and even community antibiotic resistance, which is a major health care issue [2,4-6].

A European point prevalence study in ICUs showed that 66% of patients were receiving artificial nutritional support, 42% of whom were receiving either parenteral nutrition alone (23%) or parenteral combined with enteral nutrition (19%). [7].

Although the enteral feeding route is preferred to parenteral (reduced costs of administration and reduced risk of infective complications from the intravenous line), parenteral nutrition (PN) retains an important supportive role in the management of ICU patients, many of whom cannot be fed effectively by the enteral route because of gastro-intestinal dysfunction [8].

### Glutamine

Standard amino acid formulations do not contain any of the amino acid glutamine, due to pharmaceutical stability problems. In the past glutamine was considered a non-essential amino acid therefore its omission from parenteral nutrition preparations was not considered to be a problem, as it was thought that the body would synthesise its own. Glutamine has essential roles in acid-base balance, nitrogen transport and maintaining muscle mass and function, and is an energy source for rapidly dividing cells, particularly those of the immune system and gut. As the most abundant amino acid in the body, it is now recognised that glutamine synthesis and release is insufficient to meet demands under severe metabolic stress. Glutamine must therefore be supplied from nutritional sources if levels are to be maintained. Several studies have shown that glutamine levels decrease markedly after major surgery and during critical illness. Decreased serum glutamine has been associated with immune dysfunction in animal models and death or infectious complications in septic patients. In randomised controlled trials (RCTs) amongst patients, glutamine-supplemented PN has been associated with improved nitrogen balance, higher intra-muscular glutamine levels, improved mood, enhanced immune cell function and no elevation of proinflammatory cytokine profile [9-14]. In animal models glutamine enhances intracellular glutathione (which combats free radical tissue damage) [15]. Such effects of glutamine support on the stressed immune system in the patient receiving critical care could lead to '*successful inflammation'*, i.e. the ability to combat infection, and decrease the systemic inflammatory response syndrome, where excessive free radical induced damage occurs.

Thus provision of glutamine could be of considerable benefit in metabolically stressed critically ill patients. Although the proposed benefits are biologically plausible it is unclear whether they will be obtained in practice and there is a danger that glutamine-containing PN solutions will be incorporated into practice without adequate evaluation, thus our evaluation is timely.

### Selenium

Selenium is an essential trace element found in a group of proteins known as selenoproteins and which is present in only modest amounts within standard PN solutions. Selenium, through glutathione peroxidases and thioredoxin reductase is involved in anti-oxidant defences, and also has anti-inflammatory properties [16,17] mediated by inhibition of lipid peroxidation. Selenium is also essential to the production of thyroid hormones [18]. It is noteworthy that populations in many areas of Europe, including Scotland, are relatively selenium deficient [17]. Given the widely documented immunosuppression of critical illness, and its correlation with mortality and the purported roles of reactive oxygen species in sepsis, pancreatitis, organ dysfunction and other inflammatory conditions, it is biologically plausible that enhanced selenium supplementation could also be of benefit to the critically ill ICU patient requiring parenteral nutrition.

It can be seen from the above background that both glutamine and selenium have the potential to influence the immune system, through different sites in biochemical pathways. Thus a factorial design for the proposed RCT is appropriate to test the two hypotheses.

### Systematic reviews

A systematic review of glutamine supplementation in critically ill (including following major surgery) adults [19] found 14 small RCTs reporting data from 737 patients on mortality, infectious complications, and length of hospital stay. When both parenteral and enteral routes of supplementation are combined, complications were lower in the glutamine group (risk ratio 0.81, 95% CI 0.67 to 0.99). There was also a trend towards a reduction in mortality (risk ratio 0.79, 95% CI .59 to 1.04) and reduced length of hospital stay, especially for surgical patients.

A more recent systematic review using random effects methods of meta-analysis [20] found that parenteral glutamine in critical illness was associated with a relative risk for mortality of 0.75 (95% CI 0.52 to 1.07) and for infection of 0.71 (95% CI 0.49 to 1.05). There was however, evidence of publication bias in the reporting of participants' infections. The existing evidence is suggestive of a positive role for glutamine supplementation but a further large trial is required to determine whether any differences are statistically and clinically important.

A Cochrane systematic review of selenium supplementation in critical illness, has identified seven randomised controlled trials of sodium selenite supplementation in critical illness [21]. Five trials examined the effect of additional selenium supplementation on mortality at 28 days, and showed a reduction trend in those supplemented with selenium (relative risk 0.71, 95% CI 0.43 to 1.17, random effects model). The relative risk for mortality, whenever determined, for general intensive care patients was 0.75 (95% CI 0.59 to 0.96, random effects model). Based on reported information, these were poor quality trials. Indeed, only one clearly reported concealment of allocation and a further three trials undertook intention to treat analysis.

In a systematic review of antioxidant nutrients in critical illness, Heyland and colleagues [22] found that selenium supplementation (alone and in combination with other antioxidants) may be associated with reduced mortality (RR 0.59, 95% CI 0.32 to 1.08). Clearly, a larger trial to examine the clinical effects of additional selenium supplementation in this patient group is required.,

#### Pilot Study

The purpose of the pilot study was to test the full protocol with the aim of assessing feasibility and refining PN stock management. It was carried out in two Scottish centres; Aberdeen and Edinburgh. Patients enrolled to the pilot study were recruited and processed in the same manner as the full trial and we plan to analyse these data in the final data set.

## Methods and Design

### The questions which this protocol will address

#### The questions which this trial will address

• Does the inclusion of glutamine, additional selenium or the two in combination, in a standard preparation of PN improve the outcome for critically ill patients particularly in terms of participants with infections, mortality, ICU and acute hospital stay?

• Is supplementation of PN with glutamine, additional selenium, or the two in combination cost-effective?

### Trial recruitment

The trial will involve people expected to be on intensive care and high dependency units (levels 2 and 3 care) under the care of the intensive care unit consultants for at least 48 hours, aged 16 years or over, who require parenteral nutrition and are expected to have at least half of daily nutritional requirements given by that route. Pregnant women and people whose expected stay in the UK is less than six months will not be considered for the study. Patients with severe renal failure (creatinine clearance < 10 ml/min and not on renal replacement therapy) will also be excluded.

In the case of hepatic failure, metabolism by the liver is the main route of elimination for many drugs and nutrients, but the hepatic reserve appears to be large and liver disease has to be severe before important changes occur. Routine liver function tests (LFTs) are a poor guide to the capacity of the liver to metabolise drugs, and it is not possible to predict the extent to which the metabolism of a particular drug or nutrient may be impaired. Enrolment will depend on the decision of the local physician. However, caution will be advised when:

1. A 3-fold increase in LFTs above baseline for the patient is seen.

2. Any derangement in liver synthetic function is noted.

Intensive care unit staff (doctors or nurses) based in each clinical centre will identify potential participants. A log will be kept of patients meeting the inclusion criteria, describing the reasons if they are not subsequently recruited to the trial. The recruitment procedure to be followed is detailed in the SIGNET trial handbook (version 4 15-03-06).

### Informing potential participants about the trial

If the patient is able to give consent, ICU staff (doctors or nurses) will describe the study, backing oral information with the standard study information leaflet. If, as is more likely, the patient will be unable to give consent, intensive care unit staff will describe the study to relatives of the patient, backing oral information with the standard study information leaflet.

### Consent to participate

Once eligibility has been confirmed, authorised personnel will ask if the potential participant is ready to decide whether or not to join the trial. If so, she/he will give the participant a consent form. After the doctor or nurse has checked that the consent form is understood, the nurse or doctor will invite the participant to sign the form, then will add their own name and countersign it. In the case of relatives giving assent, the same procedure will be followed using the consent form. Copies of the signed consent form and information sheet will be placed in the hospital notes. If the participant subsequently becomes able to give consent, after assent has been obtained from the relative, the study will be described to the participant using the information sheet and consent form.

If the relative is not present and cannot attend the ICU to sign the written assent within 24 hours of the patient requiring PN, but is prepared to grant assent based on the information read out to them over the phone and subsequent discussion, verbal assent will be recorded. Written record of assent at a later time will be obtained if feasible. In all cases a written information sheet will be provided when they attend or a copy sent to them by post if they are unable to attend. Separate consent forms for verbal consent have been prepared.

In the unlikely event that there is no personal legal representative (next of kin) it is possible to recruit the patient to the study, provided a professional legal representative (or equivalent in England, Wales or Ireland) has been appointed by the hospital for that person.

### Information collected at trial entry

Once a participant has agreed to join the trial, ICU staff will record on a standard form:

#### 1. Identifying and contact information

• Full name, address, telephone number

• Date of birth, age on recruitment day, sex

• NHS, hospital number and Community Health Index number (if available)

• Marital status, woman's maiden name

• Name of a 'best contact', such as a friend or relative, with contact details

• General Practitioner's contact details

#### 2. Descriptive information

• Under-nourished, normal or obese, based on subjective clinical assessment [23]

• Patient groups – medical, or surgical (including trauma))

• APACHE (Acute Physiology and Chronic Health Evaluation) II score

• SOFA (Sequential Organ Failure Assessment) score

• Severe sepsis or septic shock

• Antibiotics/anti-infectives on recruitment

This information will be sent to the Trial Office.

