### Treatment allocation

The existing central randomisation service (fully automated computerised telephone randomisation) in the Health Services Research Unit at the University of Aberdeen will be used to randomise patients. Recruiting staff will telephone the randomisation line and will be asked to key in details of identification and important prognostic factors (see below), when confirming eligibility and consent. Consent procedures will adhere to the 2003 Mental Health (Care and Treatment) (Scotland) Act. Random allocation to one of the four possible treatment combinations (see above) will be minimised on trial centre; age (<65 years or ≥ 65 years); sex; patient groups (medical or surgical (including trauma)); and, patient nutritional status (under-nourished, normal or obese – subjective clinical assessment [24]. A four digit number for that patient will be provided by the automated randomisation service, the research nurse accessing the randomisation service will then inform the centre pharmacy of this randomisation number. The trial office, based at the University of Aberdeen will have provided each pharmacy with a list of these random numbers linked to one of the four treatment allocations, thus maintaining the blinding of local investigators to the trial treatment. Figure 1 summarises these arrangements.

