#### Measures of outcome

##### Primary

• Mortality – on ICU and HDU and overall at six months

• Infections – counted as participants with new reported infections and Centres for Disease Control (CDC) confirmed infections in the first 14 days [25].

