#### Secondary sub-group analyses

Planned subgroup analyses include:

(i) Under-nourished, normal or obese;

(ii) Patient groups (medical, or surgical (including trauma));

(iii) Age <65 or ≥ 65;

(iv) Evaluation by the severity of illness, including; APACHE II and SOFA scores, above and below mean or median score; and

(v) Severe sepsis/septic shock on recruitment

Stricter levels of statistical significance (2p < 0.01) will be sought, reflecting the exploratory nature of these subgroup analyses. The Chi-squared test for heterogeneity will be used to explore any apparent differential effects.

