### Data analysis

Analysis of dichotomous outcomes will be analysed using statistical tests such the Chi-squared test. Continuous measures will be analysed using t-tests (with transformation of data to Normality if appropriate), or non-parametric equivalents. A further analysis accounting for the inter-relationship between deaths and length of stay will be undertaken, akin to that described for ventilator-free days by Rubenfield [26] mentioned earlier. This, for example, would allow the apparently short length of stays associated with early deaths to be accounted for appropriately. A significance level of 2p < 0.05 will be considered as evidence of statistical significance for the primary outcomes. Confidence intervals will also be presented where appropriate. The economic analysis will incorporate sensitivity analysis, and confidence intervals will be constructed around stochastic cost data using techniques such as bootstrapping [27].

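### The tests named for mortality are all unadjusted, although APACHE II and severe sepsis are recorded at entry and not minimised on; adjusting for them would buy modest precision at almost no cost

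*Protocol article*

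**What the plan says.** All references are to the protocol article.

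- **Outcome.** Under Measures of outcome, Primary, the first entry is "Mortality – on ICU and HDU and overall at six months".
- **Test.** Data analysis says: "Analysis of dichotomous outcomes will be analysed using statistical tests such the Chi-squared test". Continuous measures get t-tests or non-parametric equivalents. No covariate-adjusted model is named for any clinical outcome.
- **Severity at entry.** Section 2, Descriptive information, lists "APACHE (Acute Physiology and Chronic Health Evaluation) II score", the SOFA score and "Severe sepsis or septic shock" among the items recorded when a patient joins.
- **Allocation.** Under Treatment allocation, patients are "minimised on trial centre; age (<65 years or ≥ 65 years); sex; patient groups (medical or surgical (including trauma)); and, patient nutritional status". No severity measure is included.
- **Later use of severity.** Secondary sub-group analyses gives "Evaluation by the severity of illness, including; APACHE II and SOFA scores, above and below mean or median score" and "Severe sepsis/septic shock on recruitment". No other analytic role is named for these variables.

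**The concern.** In a critically ill population, severity at entry can be expected to carry information about who dies. The trial collects that information before allocation but, as described, does not use it in the mortality comparison.

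This matters more for mortality than for infection. The Power calculation section sizes the trial on infection and gives no calculation for mortality, where precision is scarcer (shown in the working). A test that ignores a prognostic baseline variable gives up some of that precision. It also returns an estimate that moves with any severity difference that happens to arise between the groups.

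Prespecification matters too. The study statistician supplies the confidential interim analyses (The Data Monitoring Committee) and also carries out the formal analysis (The Trial Office). Covariates chosen late, or only once an imbalance has been noticed, would be open to challenge.

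**Working it through.** **1. The plan's own figure.** For infection, 50% v 35%, 80% power, two-sided 5%, pooled variance:

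n per arm = [1.96·√(2·0.425·0.575) + 0.842·√(0.50·0.50 + 0.35·0.65)]² / 0.15² = (1.370 + 0.582)² / 0.0225 ≈ 169.3, so 170 per arm and 340 in total.

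The stated 340 reproduces, but it concerns infection only.

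**2. Unadjusted power for mortality.** The target of 500 gives about 250 v 250 on each factorial margin. The article gives no six-month mortality rate. For illustration, take the 30% hospital mortality from Background and the relative risk of 0.75 from the parenteral glutamine review under Systematic reviews. For 30% v 22.5%:

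z = (0.075 − 1.96·√(2·0.2625·0.7375/250)) / √((0.30·0.70 + 0.225·0.775)/250) = (0.0750 − 0.0771)/0.0392 = −0.05, so power is 48%.

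The same formula gives 65% for 40% v 30% and 73% for 45% v 33.75%.

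**3. Gain from adjustment.** Simulation, 250 v 250, 3,000 trials per setting. The Chi-squared test is compared with logistic regression on treatment plus one standardised severity score. The log-odds SD of the score is **assumed** to be 0.55, 0.75 or 1.0 (AUC about 0.65, 0.69, 0.74). The last column is ((1.96 + z_adj)/(1.96 + z_unadj))² − 1, where z is the normal quantile of the power.

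| True mortality | Assumed AUC | Unadjusted | Adjusted | Gain | Equivalent extra patients |
|---|---|---|---|---|---|
| 35% v 25% | 0.65 | 68% | 70% | 2 | 5% |
| 35% v 25% | 0.69 | 68% | 72% | 4 | 10% |
| 35% v 25% | 0.74 | 68% | 75% | 7 | 18% |
| 40% v 30% | 0.65 | 64% | 67% | 3 | 7% |
| 40% v 30% | 0.69 | 66% | 70% | 4 | 10% |
| 40% v 30% | 0.74 | 66% | 73% | 7 | 18% |

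Each simulated power has a standard error of about √(0.68·0.32/3000) = 0.9 points. That is why the unadjusted column varies around the formula value of 65% for 40% v 30%.

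**4. A second simulation over a wider range.** 2,500 trials per setting, relative risk 0.75, assumed AUC 0.65 / 0.72 / 0.78:

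- 30% control mortality: unadjusted 49.0 / 48.5 / 47.0%, adjusted 50.5 / 52.6 / 57.0%.
- 45% control mortality: unadjusted 72.5 / 72.8 / 73.8%, adjusted 75.6 / 79.2 / 83.6%.
- Variance of the risk difference falls by about 5%, 12 to 14% and 21 to 22%.
- Type I error: unadjusted 4.7 to 6.1%, adjusted 4.9 to 5.4%. Both are near 5%.

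**5. Chance imbalance.** With an **assumed** APACHE II SD of 7, the standard error of the difference in means is 7·√(4/500) = 0.63 points. The chance of a difference of 1 point or more is 2·(1 − Φ(1/0.63)) ≈ 11% per comparison. At an **assumed** 0.1 log-odds per point, and mortality near 30%, 1 point moves mortality by about 0.1·0.30·0.70 = 2.1 percentage points.

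For scale, the standard error of the risk difference is √((0.35·0.65 + 0.25·0.75)/250) = 4.1 points for 35% v 25%, and 4.2 points for 40% v 30%. A 1-point imbalance is therefore about half a standard error, and is already part of it. In the second simulation, each 0.1 SD of imbalance moved the unadjusted risk difference by 1.1 to 2.4 points and the adjusted one by about zero.

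**The case against.** The best case for leaving the plan alone has four parts.

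- **The article does not forbid adjustment.** Its wording makes Chi-squared an example, and covariates are often left to an analysis plan, which is not shown here. A reader might infer that the trial has committed itself to an unadjusted mortality analysis; the text does not go that far. What stands is narrower: the article does describe its methods, every clinical test it names is unadjusted, and the only analytic role it names for severity is in subgroups.
- **The unadjusted test is sound.** A reader might infer that severity imbalance biases the mortality result or cannot be told apart from treatment. The design does not support that. Randomisation balances severity on average, the Chi-squared standard error covers the chance variation, and simulated type I error is near 5%. For the same reason it would be wrong to say that nothing in the design balances severity. This part stands in full.
- **The gain is assumed and can be small.** The article gives no discrimination, SD or slope for APACHE II. At AUC 0.65 the gain is only about 2 to 3 points, not far above simulation error. This also stands.
- **Infection is the endpoint used for sample size, and adjustment does not rescue mortality.** That is true: over AUC 0.65 to 0.74 power stays below 80%, and in the wider range only 45% control mortality with AUC 0.78 exceeds it. But mortality is still listed as primary, and recovering part of a shortfall from data already held is worth doing.

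**Conclusion.** The point holds as a matter of efficiency, not validity. The plan names a correct but less precise comparison for a primary outcome, although baseline severity data that could sharpen it are already collected.

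The expected gain is roughly 2 to 7 percentage points of power for 250 v 250 with AUC between about 0.65 and 0.74, equivalent to about 5% to 18% more patients. A weaker severity score would give less and a stronger one more. These figures rest on assumed prognostic strength, assumed mortality rates and a single severity covariate. What the article itself establishes is which variables are recorded, which are minimised on and which tests are named; the size of the loss is illustrative.

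**What to change.** In Data analysis, state that the main mortality analysis for each factorial margin is a logistic model adjusted for:

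- APACHE II at entry, as a continuous variable;
- severe sepsis or septic shock at entry;
- the minimisation factors: age, sex, medical or surgical group, nutritional status and centre.

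The minimisation factors belong in the model because they shaped the allocation and no named test uses them. Report the adjusted odds ratio together with a standardised risk difference, since the adjusted odds ratio alone is not on the scale of the crude comparison. Give the unadjusted Chi-squared result alongside.

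The cost is a sentence or two of text, slightly more analysis work and a simple prespecified rule for missing baseline scores, whose completeness the article does not report. Neither allocation nor data collection changes, so the step remains open with recruitment under way. The covariates should be fixed without reference to the interim comparisons.
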